## Abstract

**Background:**

Music therapy is frequently used as a palliative therapy. In consonance with the goals of palliative care, the primary aim of music therapy is to improve people’s quality of life by addressing their psychological needs and facilitating communication. To date, primarily because of a paucity of robust research, the evidence for music therapy’s effectiveness on patient reported outcomes is positive but weak. This pilot and feasibility study will test procedures, outcomes and validated tools; estimate recruitment and attrition rates; and calculate the sample size required for a phase III randomised trial to evaluate the effectiveness of music therapy in improving the quality of life of palliative care patients.

**Methods:**

A pilot randomised controlled trial supplemented with qualitative methods. The quantitative data collection will involve recruitment of >52 patients from an inpatient Marie Curie hospice setting over a 12-month period. Eligibility criteria include all patients with an Eastern Cooperative Oncology Group (ECOG) performance status of 03− indicating they are medically fit to engage with music therapy and an Abbreviated Mental Test (AMT) score of ≥7 indicating they are capable of providing meaningful informed consent and accurate responses to outcome measures. Baseline data collection will include the McGill Quality of Life Questionnaire (MQOL); medical and socio-demographic data will be undertaken before randomisation to an intervention or control group. Participants in the intervention arm will be offered two 30–45 min sessions of music therapy per week for three consecutive weeks, in addition to care as usual. Participants in the control arm will receive care as usual. Follow-up measures will be administered in 1, 3 and 5 weeks. Qualitative data collection will involve focus group and individual interviews with HCPs and carers.

**Discussion:**

This study will ensure a firm methodological grounding for the development of a robust phase III randomised trial of music therapy for improving quality of life in palliative care patients. By undertaking the pilot and feasibility trial under normal clinical conditions in a hospice setting, the trial will result in reliable procedures to overcome some of the difficulties in designing music therapy RCTs for palliative care settings.

**Trial registration:**

Clinicaltrials.gov Identifier: NCT02791048

**Electronic supplementary material:**

The online version of this article (doi:10.1186/s40814-016-0111-x) contains supplementary material, which is available to authorized users.

## Background

Music therapy has increasingly been implemented in a range of healthcare settings, including oncology, dementia and intensive care [1–3]. Music therapy is among the two most common forms of complementary therapy provided in hospices [4], with inclusion of music therapy in palliative care settings having a long tradition stemming back to the 1970s [5]. With the World Health Organisation definition of palliative care as ‘the active total care of patients’ where the ‘control of…psychological, social and spiritual problems is paramount’ [6], widespread provision of music therapy is consonant with the holistic approach which distinguishes palliative care from other areas of healthcare.

In terms of palliative care provision, figures for 2006 show there were 193 specialist inpatient units, 295 home care services, 314 hospital-based services, 234 day care services and 314 bereavement support services across England, Wales and Northern Ireland [7]. While there are no figures available for the existing provision of music therapy in palliative care services as a whole, a survey by Daykin et al. [8] showed that music therapy is still an emerging therapy within cancer care across the UK compared to more established interventions such as art therapy. This survey showed that the majority of music therapy provision was funded externally by the NHS, or in a small number of cases from internal funding. Music therapy was also more likely to be used in settings were complementary and alternative therapies were already in place, suggesting a trend towards the use of music therapy as an additional supportive service rather than replacing existing services. There are currently no guidelines in place for the use of music therapy in palliative care. This highlights the need for a stronger evidence base that takes due cognisance of benefits and risks to help inform future music therapy provision [9].

Music therapy entails the use of music to achieve individual goals in the context of a therapeutic relationship with a professional music therapist [10]. In the UK, music therapists are trained to master’s level and are registered with Health and Care Professions Council as allied health professionals. Music therapy aims to improve the quality of life of palliative care patients by relieving physical and psychological symptoms, facilitating communication and alleviating spiritual or existential concerns [11].

Music therapy approaches range from ‘receptive’ to ‘recreative’ depending on the patient’s level of physical limitations. Receptive approaches are more passive in terms of listening to music played by the therapist, while recreative approaches can involve the patient singing or playing their favourite music alongside the therapist [12]. One of the most common approaches for palliative care patients is legacy work, whereby the therapist helps patients produce a compilation of songs that have meaning for them to leave for family and friends [13]. Irrespective of the approach, music therapy aims to support and improve physical, psychological and existential well-being [14]. With goals mirroring those of palliative care, music therapy research within this population is both necessary and of great importance to supportive palliative care initiatives.

Most palliative care referrals for music therapy are in relation to pain and quality of life [15]. A recent systematic review of randomised controlled trials reported significant improvements in pain experienced by palliative care patients receiving music therapy [16]. Although the most recent Cochrane review on music therapy for end-of-life care, published in 2010, recommended more research of high quality to support the effectiveness of music therapy for improving quality of life [17], there have been no additional high-quality studies evaluating this outcome within the last 5 years [16]. Several challenges to conducting music therapy randomised controlled trials (RCTs) in palliative care have also been identified, including high levels of attrition, the need for flexibility in time commitment and inclusion of family members if desired and provision of a standardised yet tailored intervention [17]. Process evaluation using qualitative methods is recommended for future trials to aid in identifying factors which contribute to or limit the effectiveness of music therapy interventions [17].

Based on promising findings regarding the benefits of music therapy for improving the quality of life, more research is needed to produce robust evidence of effectiveness in the field of palliative care where music therapy is already in widespread use and in high patient demand [18, 19]. Furthermore, given that research in music therapy and in palliative care are fraught with challenges [20, 21], pilot and feasibility studies are required to establish the most robust study design and processes to facilitate high-quality research in this area [22].

## Methods/design

### Trial aims and objectives

This study aims to establish the feasibility of and to pilot an RCT to evaluate the effectiveness of music therapy in improving the quality of life and inter-familial communication in palliative care patients. The trial will be conducted under normal clinical conditions to test procedures, outcomes and validated tools; estimate recruitment and attrition rates; and calculate the sample size required for a phase III randomised trial. Qualitative data collection with carers and health care practitioners (HCPs) will supplement this further by examining if music therapy leads to an improvement in inter-familial communication and determining which processes help or hinder the implementation of music therapy within a hospice setting. This protocol follows the SPIRIT guideline for writing protocols (see Additional file 1, SPIRIT 2013 Checklist).

### Primary outcome

The main aim of the study is to evaluate the feasibility of administering the McGill Quality of Life Questionnaire (MQOL) [23], reported to have the best clinometric quality rating, content validity, construct validity and internal consistency of reviewed quality of life questionnaires [24]. We will also assess the viability of delivering a 3-week music therapy intervention, along with using recruitment and attrition rates to determine the sample size required for a phase III randomised controlled trial.

### Secondary outcomes

The potential effectiveness of music therapy upon quality of life at week one (one to two music therapy sessions), week three (after completion of the music therapy course) and week five (two weeks after completion of music therapy)The effect of music therapy upon inter-familial communicationThe effect of contextual factors upon the implementation and sustainability of music therapy in a palliative care setting

### Intervention

Participants will be randomly assigned to two groups. Patients assigned to the control group will receive usual care only from the hospice multidisciplinary team. The dose and frequency of usual care will be as deemed appropriate by the hospice practitioner in charge of their treatment. As music therapy is not part of usual care within this hospice, the control group participants will be offered two sessions of music therapy upon completion of their time in the study. The researcher will notify the music therapist each time a participant has finished their third and final study visit. The music therapist can then offer those in the control group their music therapy sessions when a slot becomes available (see the participant flow chart in Additional file 2).

In addition to the usual care described above, patients assigned to the experimental group will receive music therapy in an individual setting, delivered by a trained music therapist. Music therapy will be conducted for up to 45 min twice a week. A total of six sessions will be offered, with the aim of completing at least four sessions. Patient’s needs will be identified by the music therapist during the first session, guided by preliminary discussions with the hospice clinical team and by the patient’s own assessment of what needs are most important to them. The musical equipment used will include accessible instruments provided by the music therapist.

As recommended by our PPI (Patient and Public Involvement) collaborators on this protocol, patients can choose to have their carer present during the intervention as time together is precious. Patient’s written informed consent to have their carer present will be obtained by the hospice clinician during recruitment. Carers will only be observing the music therapy sessions and will not be directly involved.

In palliative care, the music therapeutic approach used is a creative process of musical interaction where the client engages while singing or playing, listening to music or extemporaneously creating a melody, rhythm, song or instrumental piece. In the sessions, the music therapist uses music in various formats to meet the patients’ specific needs. In doing so, they ‘make use of the therapeutic relationship established with the patient to meet clinical goals and employ a systematic therapeutic process that includes assessment, treatment and evaluation’ [17].

In terms of ‘dose’ of music therapy, previous studies in palliative care patients have shown that a short course, consisting of two or more sessions, is effective and appropriate for this population [25, 26]. While the content of the sessions will be influenced by each patient’s needs, interests, preferences and energy level and adapted accordingly in the moment, the music therapist will complete an intervention manual [27] at the end of each session, which will include the details on who chose the music and what strategy was used (i.e. music listening, active music-making, improvising, legacy work), along with strategies to enhance treatment fidelity (how the intervention was monitored for consistency). This will aid transparent reporting, along with guiding the development of a standardised protocol for use across sites in the main trial.

As with the control group, the dose and frequency of usual care will be as deemed appropriate by the hospice professional in charge of their treatment.

### Study setting

Participants will be recruited from the inpatient unit and day hospice at an 18-bed specialist palliative care unit in Northern Ireland.

### Trial design

A UK-based, single-centre, pilot RCT will involve two parallel arms, one receiving individual music therapy in addition to usual care, and the other receiving usual care only. It is not possible to blind patients to treatment allocation, but the researcher administering the study measures will be blinded up until the completion of the first follow-up visit; after which time, the researcher will invite patients and carers to talk freely about their experience of music therapy if they have been in the intervention arm of the trial. In order to maintain a level of blinding, we propose to have an outcome adjudicator conduct a data check of data entry and a statistician conduct data analysis, both blinded to treatment allocation. As only the researcher will be blinded to the intervention, we cannot foresee circumstances which will require unblinding. This study will employ mixed methods to meet all study objectives.

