#### Secondary outcomes

To assess the potential effectiveness of music therapy, data will be analysed using the Statistical Package for Social Sciences, v20. The change in the outcome variable from baseline to 1 week, 3 weeks and 5 weeks, will be compared between the experimental and control group using analysis of covariance [35]. To detect differences within groups, repeated measures ANOVAs will be utilised. As this pilot study does not include a formal power calculation, confidence intervals will be clearly stated with any estimates, and findings should be interpreted with caution. The principle of intention to treat analysis will be performed blind to treatment allocation. In line with the intention-to-treat principle, patients who attend fewer sessions will not be excluded from data analysis. Qualitative methods, in particular interviews and focus groups, will be used to assess inter-familial communication and contextual factors.

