### Data management

Data will be collected on a study-specific case report form (CRF) starting at the time of recruitment. This form will collect socio-demographic data at baseline, along with details of current treatments and medications which will be collected at all four study visits—randomisation (baseline), week one (after one to two music therapy sessions), week three (after final music therapy session) and at week five (end of trial). Data will be entered anonymously onto an encrypted file server which will be stored in a secure office. Recommendations for managing attrition and access data when conducting palliative care research will be followed [34]. Different types of attrition will be reported to include attrition due to death (ADD), attrition due to illness (ADI) and attrition at random (AAR). Consideration will also be given to how timing of data collection affects attrition rates. Qualitative data will be managed using the Nvivo V.11 software.

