### Qualitative data collection

(i)Carer interviews

Design

Carer interviews aim to assess whether music therapy improves inter-familial communication within a palliative care population. In the absence of a validated tool to measure this outcome, an interview topic guide will be developed by the research team. Interviews will be digitally recorded and transcribed verbatim, at which point recordings will be deleted. Confidentiality will be ensured by removing all identifying information from the transcripts.

Carers who are newly bereaved during the trial will be excluded from the study. Sample size will be dictated by data saturation though it is estimated that 26 carers will be recruited. Carers who chose to sit in on the music therapy sessions will be given an invitation letter and information sheet by the music therapist after the patient’s second music therapy session (end of week one). Carers will also have the opportunity to take part in another interview after the patient’s final music therapy session (week three) if they wish to. For those carers who chose not to sit in on music therapy sessions, an invitation letter and information sheet will be left with their loved one to give to them on their next visit.

Carers who return a Notification of Interest Form to the music therapist or member of hospice staff will be contacted by the researcher and given the opportunity to ask questions about the study, at which point they can decide to opt out or provide written informed consent.

Interviews will take place at the participant’s home if they choose, or in a private room at the hospice. It is anticipated that the interview will last for 40–60 min. The same ethical and data analysis procedures will be conducted as outlined for focus group data. If carers have a concern or become upset about any aspect of the study, they can speak to the researcher or one from the study team. If appropriate, they will ensure that the carer will be given the opportunity to talk any issues through with the hospice care team.(ii)Process evaluation

Design

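### A planned conversation unblinds the researcher who administers the MQOL after week 1, so the week-3 and week-5 assessments are collected unblinded

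*Protocol article*

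**What the plan says.** Under Trial design, the protocol article accepts that patients cannot be blinded and states that "the researcher administering the study measures will be blinded up until the completion of the first follow-up visit". It then names the event that ends the blinding: "the researcher will invite patients and carers to talk freely about their experience of music therapy if they have been in the intervention arm". To preserve some blinding, it adds a blinded check of data entry and a blinded statistician. The same paragraph says that no circumstances requiring unblinding are foreseen.

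The visit schedule is in the Abstract (Methods): "Follow-up measures will be administered in 1, 3 and 5 weeks". The list of secondary outcomes places week 3 after completion of the course and describes the last assessment as "week five (two weeks after completion of music therapy". The analysis of secondary outcomes compares between arms "The change in the outcome variable from baseline to 1 week, 3 weeks and 5 weeks", using analysis of covariance.

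Allocation and randomisation has an administrator pass the allocation to the music therapist so that the researcher stays blind. It sets no time limit on this.

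**The concern.** Patients know their arm and the MQOL is a subjective self-report. The person who administers it is therefore the only party at the point of measurement who can be kept blind. An administrator who knows the allocation, and who has just invited the patient to discuss the therapy, may prompt, help with answers or invite socially desirable responses, and this would happen in one arm only. Patients with communication difficulties are eligible if they can indicate their responses, so help with answering is a realistic possibility.

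At stake are the between-arm estimates at the end of the course and two weeks later. These are the two time points at which an effect of the full course could be seen. A phase III trial that copied the procedure would inherit the weakness.

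**Working it through.** No power or precision calculation applies. The point concerns who knows the allocation and when, so the check sets the blinding text against the visit, analysis and interview schedules.

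1. **When blinding ends.** Blinding lasts until the first follow-up visit is complete (Trial design). Follow-up visits are at weeks 1, 3 and 5 (Abstract, Methods). Data management lists the same three after baseline, making four visits. The first follow-up is therefore week 1. The Intervention section refers to a third and final study visit, which agrees if it means the third follow-up; week 1 is the first follow-up on either count.

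2. **Status of each follow-up MQOL under the plan.**

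| Assessment | Position in the course | Administrator |
|---|---|---|
| Week 1 | After one to two sessions | Blind |
| Week 3 | End of course | Not blind |
| Week 5 | Two weeks after the course | Not blind |

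Count: 1 of 3 blind, 2 of 3 not blind. All three enter the between-arm comparison.

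3. **Whether the stated safeguards reach the problem.** The data-entry check compares records with what was written down, and the statistician analyses what was entered. Both come after the patient has answered, so neither can remove an influence on the answer itself.

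4. **Whether the timing is needed for patients.** The qualitative data come from carers (interviews) and health care practitioners (focus groups). No qualitative data set from patients is listed that requires this conversation before week 5, and no reason for the timing is given. Feedback from patients on the burden of the MQOL is collected at each visit, but that concerns the questionnaire and not the therapy.

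5. **Whether the timing is needed for carers.** Here it partly is. Carers are invited after the patient's second session (end of week one) and may be interviewed again at week 3. Newly bereaved carers are excluded and a 30% attrition allowance is planned, so waiting until week 5 could lose interviews that serve a listed secondary outcome.

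6. **Consistency.** Routing the allocation around the researcher, and foreseeing no need to unblind, both fit poorly with an unblinding that is scheduled in the same protocol.

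7. **After the change.** If the patient conversation follows the week-5 MQOL and someone else sees the carers before then, the plan itself no longer unblinds the administrator at any of the 3 follow-ups. Accidental disclosure by patients remains possible.

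**The case against.** The strongest defence is that this is a disclosed choice in a pilot. The primary outcomes are the feasibility of the MQOL, the viability of the intervention, recruitment and attrition. Progression depends on recruitment, and the phase III power calculation is described as using recruitment and attrition figures. None of these needs a blinded between-arm estimate. Effectiveness is secondary, called potential, and reported with confidence intervals and an explicit caution. The patients who answer the MQOL are unblinded in any case, so a blind administrator removes only part of the bias. All of this stands. It limits the weight of the point but does not justify a loss of blinding that is avoidable for patients.

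The carer part of the defence also stands. Those interviews cannot simply be postponed, and the protocol does not say whether the experienced qualitative researcher who runs the focus groups is a different person from the one who administers the MQOL.

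Two stronger readings are tempting and are not supported.

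- A reader might infer that week 1 is exposed as well, because "Carers who return a Notification of Interest Form to the music therapist or member of hospice staff will be contacted by the researcher" and because the case report form takes "details of current treatments and medications which will be collected at all four study visits". But Trial design places the invitation to talk after the week-1 visit, and a carer must return a form before the researcher makes contact. Nothing puts that contact before the week-1 MQOL. The form is not shown, and the text does not say that current treatments include trial music therapy.
- A reader might want to express the bias as a loss of confidence interval coverage. The document gives no size for an administrator's influence, so any such figure would only reflect the value assumed.

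**Conclusion.** The point holds as a matter of design. Under the plan, 2 of 3 follow-up MQOL assessments (week 3, at the end of the course, and week 5) are collected by an administrator who knows the allocation, and the stated safeguards cannot correct bias that arises at measurement. The wording also conflicts with the intention elsewhere to keep the researcher blind.

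The conclusion rests on two readings of the text: that the first follow-up visit is week 1, and that the same researcher administers all three follow-ups, since no other administrator is named. The direction and size of any bias are unknown. The consequence is confined to the secondary effectiveness estimates; the primary feasibility outcomes are not undermined. The change is worth making because its patient part costs almost nothing.

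**What to change.** - Keep the MQOL administrator blind through the week-5 MQOL. Move the invitation to patients to talk about music therapy to after that MQOL, or to withdrawal if earlier.
- At each visit, complete the MQOL before anything else is asked.
- Leave carer interviews at their planned times. Assign carer contact and interviews before week 5 to an existing team member who does not administer the MQOL, provided the sponsor confirms that one is available.
- If none is available, record which MQOL assessments followed carer contact and report those as unblinded.
- Bring the blinding text under Trial design and under Allocation and randomisation into agreement.

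**Cost.** For patients, this means protocol wording and a change in the order of tasks. Those who die before week 5 will not have the conversation. For carers, the cost depends on staffing that the document does not describe: an estimated 26 carers, some interviewed twice and some at home. The gain is partial, because unblinded patients may still reveal their allocation.
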